#### Economic analysis

Service utilisation and the out-of-pocket expenditures of the participants and the infants (costs for seeing a doctor or other health-care provider, admission to hospital, medicines, tests and extra help at home) will be collected in both trials (at the 3- and 6-month postnatal follow-ups). The data collected through the CSRI will be used to calculate service costs and total costs of care for each participant. Unit costs of services itemised in the CSRI – such as cost per outpatient visit – will be based on locally conducted health facility costing exercises. Service cost data will subsequently be linked to primary and secondary study outcomes, in particular depression and disability summary scores (PHQ-9 and WHO-DAS, respectively), to assess issues around the value or cost-effectiveness of the task-shifting intervention. In the event that dominance is not shown, i.e. the THPP intervention is more effective but the costs are also more than in the EUC group, incremental cost-effectiveness ratios will be computed, together with their confidence intervals (using bootstrapping techniques to overcome the expected skewness of the cost data). Results will be plotted on a cost-effectiveness plane and presented as cost-effectiveness acceptability curves to show the probability of the intervention being cost-effective at a range of willingness-to-pay threshold levels. A sensitivity analysis will be conducted to take account of uncertainty and imprecision in the measurements, including multiple imputation models for missing values.

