**Methods/Design:**

THPP is evaluated with two randomised controlled trials: a cluster trial in Rawalpindi, Pakistan, and an individually randomised trial in Goa, India. Trial participants are pregnant women who are registered with the lady health workers in the study area in Pakistan and pregnant women attending outpatient antenatal clinics in India. They will be screened using the patient health questionnaire-9 (PHQ-9) for depression symptoms and will be eligible if their PHQ-9 is equal to or greater than 10 (PHQ-9 ≥ 10). The sample size will be 560 and 280 women in Pakistan and India, respectively. Women in the intervention arm (THPP) will be offered ten individual and four group sessions (Pakistan) or 6–14 individual sessions (India) delivered by a peer (defined as a mother from the same community who is trained and supervised in delivering the intervention). Women in the control arm (enhanced usual care) will receive health care as usual, enhanced by providing the gynaecologist or primary-health facilities with adapted WHO mhGAP guidelines for depression treatment, and providing the woman with her diagnosis and information on how to seek help for herself. The primary outcomes are remission and severity of depression symptoms at the 6-month postnatal follow-up. Secondary outcomes include remission and severity of depression symptoms at the 3-month postnatal follow-up, functional disability, perceived social support, breastfeeding rates, infant height and weight, and costs of health care at the 3- and 6-month postnatal follow-ups. The primary analysis will be intention-to-treat.

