### Power calculations

The power calculations for both trials are given in Table 4 and the assumptions are given below.

**Table 4 Tab4:** Power calculations: SHARE trials

Assumptions	Pakistan	India
Unit of randomisation	Villages (stratified within union councils)	Individual (stratified by urban/rural area of residence)
Intra-cluster correlation	0.07 in the intervention arm	0.05 in the intervention arm (30 therapists; within-therapist clustering) [22, 32, 33]
	0.05 in the control arm (between-village clustering) [22]	
Loss to follow-up over 6 months	20 % [22]	15 % [8]
Allocation ratio (intervention/control)	1:1	1:1
Number of participants	560 (14 per village; 40 village clusters)	280
Outcome	Power	
Remission at 6 months (PHQ-9 < 10) of 65 % in the intervention arm vs 45 % in the control arm [22]	90 %	86 %
Remission at 6 months (PHQ-9 ≤ 5) of 38 % in the intervention arm vs 22 % in the control arm [22]	81 %	74 %
Depression severity at 6 months (PHQ-9 score) – effect size 0.4	90 %	84 %

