#### SHARE Pakistan

The power calculations assume the following:That 40 village clusters are randomised with a 1:1 allocation ratio, stratified within 11 union councils (i.e. a stratified cluster randomised trial).Intra-cluster correlation (ICC) of 0.07 in the intervention arm, and 0.05 in the control arm, to allow for between-village cluster correlation. This is a conservative estimate based on the Rahman et al. THP trial [22] in a similar population, where ICC of 0.04–0.09 was observed between union councils (which were the cluster units). We would expect a substantially lower ICC between villages within a union council.That 14 participants are recruited per village cluster, with loss to follow-up of 20 % over 6 months (conservative, based on the Rahman et al. trial, which had 10 % loss to follow-up of mothers at 6 months) [22].

The sample size of 560 participants recruited provides 90 % power to detect a difference in remission at 6 months of 65 % in the intervention arm and 45 % in the control arm. This sample size also provides 90 % power to detect an effect size of 0.4 for the continuous outcomes.

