#### SHARE India

The power calculations assume the following:There are 25–40 peers in the intervention arm.ICC of 0.05 is based on the Rahman et al. THP trial. This may be conservative as the CoBalT trial found within-therapist clustering of only 0.0027 [32] and MANAS had 0.02 [33]. We allowed for within-therapist clustering and variations in experience, competence and delivery of the intervention by the therapist. Patients randomised to one therapist may have outcomes more similar to each other than patients randomised to a different therapist. We based the estimate of the within-therapist ICC on previous studies (CoBalT trial and MANAS).Loss to follow-up of 15 % over 6 months (based on the Goa postnatal depression cohort study, which reported an attrition rate of 13 % over 6 months) [8].Equally sized groups (1:1 allocation ratio) due to the relatively small ICC.Remission rates at 6 months of 45 % in the control arm and 65 % in the intervention arm (based on the Rahman et al. THP trial, which had recovery rates of 47 % and 77 % respectively; slightly lower recovery rates are assumed as the intervention is being delivered by peers).

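### The planned bootstrap interval on the ICER has no safeguard for an effect difference that may be zero: usual forms then print a finite upper limit where none exists, so the interval belongs on net benefit

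*Protocol article*

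**What the plan says.** The Economic analysis section links costs to the study outcomes, "in particular depression and disability summary scores (PHQ-9 and WHO-DAS, respectively"). The condition for a ratio is "In the event that dominance is not shown, i.e. the THPP intervention is more effective but the costs are also more than in the EUC" arm. In that event "incremental cost-effectiveness ratios will be computed, together with their confidence intervals (using bootstrapping techniques to overcome the expected skewness of the cost data"). No further condition is set, such as an effect difference distinguishable from zero. The section does not give the type of bootstrap interval, its confidence level or the way replicates are ordered. It then adds two displays of joint uncertainty: "Results will be plotted on a cost-effectiveness plane and presented as cost-effectiveness acceptability curves".

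The likely precision of the effect difference can be read from Table 4 under Power calculations. The line "Depression severity at 6 months (PHQ-9 score) – effect size 0.4" carries a stated power of 90% in Pakistan and 84% in India.

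**The concern.** The only reason given for bootstrapping is that costs are skewed. The harder problem with an ICER is its denominator. If the effect difference could be zero or negative, the ratio is not an ordered scale of value. A replicate in which THPP is dearer and less effective is the worst result possible, yet its ratio is negative and sorts below every favourable ratio. A replicate with a tiny positive effect gives a huge positive ratio. Any interval built by sorting raw ratios mixes these up.

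Cost-effectiveness is one of the two stated aims. At stake is an interval that shows a finite upper limit when the data set none and, where costs are clearly higher, a negative lower limit that a reader may take for possible cost saving.

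**Working it through.** **1. Reproduce Table 4 for the PHQ-9 score** (effect 0.4 SD, two-sided 5%). Inputs: "The sample size will be 560 and 280 women in Pakistan and India, respectively"; for India, "Loss to follow-up of 15 % over 6 months"; for Pakistan, "That 14 participants are recruited per village cluster, with loss to follow-up of 20 % over 6 months"; the ICCs in Table 4. SE = √[(DE_int + DE_con)/n per arm], with DE = 1 + (m − 1) × ICC.

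- Pakistan: n = 560 × 0.80/2 = 224 per arm and m = 14 × 0.80 = 11.2. DE = 1 + 10.2 × 0.07 = 1.714 and 1 + 10.2 × 0.05 = 1.510. SE = √(3.224/224) = 0.120. Power is 91.5% by the normal approximation and 90.1% by t with 38 df (stated 90%).
- India: n = 280 × 0.85/2 = 119 per arm, 30 peers, m = 3.97. DE = 1 + 2.97 × 0.05 = 1.148 and 1. SE = √(2.148/119) = 0.134. Power is 84.5% (stated 84%).

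The stated powers are sound and can be used to size the problem.

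**2. How often is the effect non-significant?** Expected z = 1.96 + z(power): 1.96 + 1.28 = 3.24 (Pakistan) and 1.96 + 0.99 = 2.95 (India). P(non-significant) = Φ(1.96 − z) = 10% and 16%. If the true effect were half as large (an illustration; the article does not assume it), Φ(1.96 − z/2) = 63% and 69%. These are shares of all trials. How many of them would also show higher costs, and so trigger an ICER, cannot be derived from the article.

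**3. What the interval does in that case.** India SE implied by the stated power: 0.4/2.95 = 0.135 SD. Take an observed effect of 0.2 SD, so z = 0.2/0.135 = 1.48, and P(replicate effect < 0) = Φ(−1.48) = 6.9%. Assume a cost difference of 3 SE, normal differences and no cost–effect correlation. In cost SEs per SD of effect, the ICER is 3/0.2 = 15.

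| Interval | Lower | Upper |
|---|---|---|
| Percentile, raw ratios | −98 | 135 |
| Bias-corrected, raw ratios | −30 | 305 |
| Ordered by quadrant | 3.9 | none |

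Only 0.13% of replicates are cheaper; 98% of the negative ratios are dearer and less effective.

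**4. Vary the assumed cost difference** (effect still 0.2 SD). The dearer-and-less-effective share of the negative ratios is about 29% at 1 SE, 76% at 2 SE, 92% at 2.5 SE and 98% at 3 SE. At 1 SE about 15% of replicates are genuinely cheaper and more effective, so a negative lower limit is then legitimate. The finite upper limit is false throughout, because more than 2.5% of replicates are dearer and less effective in every case.

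**5. Vary the effect, with an actual bootstrap** (119 per arm, lognormal costs, assumed cost difference 30 units, individual resampling).

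| Effect (SD) | Replicates with effect < 0 | Raw-ratio percentile | Ordered by quadrant |
|---|---|---|---|
| 0.4 | 0.0% | 37.5 to 174.5 | 37.4 to 174.5 |
| 0.3 | 0.4% | 45 to 358 | 47 to 389 |
| 0.2 | 4.0% | −544 to 1169 | 59 to no limit |
| 0.1 | 19% | −3234 to 2958 | 80 to no limit |

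At 0.4 SD there is no practical difference. Near the significance boundary the raw interval is already too short: in normal draws with the effect at 2.2 SE and costs at 4 SE it is 0.60 to 9.37, against 0.72 to 16.97 ordered. Skewed costs are present in the bootstrap and resampling handles them; the failure comes from the denominator.

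**The case against.** The strongest reply is that the article says only that bootstrapping will be used. A reader might infer that the plan itself ranks dearer and less effective replicates as the best ratios. The text does not support that: it names neither a percentile interval nor an ordering rule, intervals ordered by quadrant exist, and an article may leave such detail to a fuller plan that is not shown. This stands as a limit on the claim. What remains is what the article does fix: an interval on the ratio, triggered without regard to the precision of the effect, and justified by a reason that does not touch the denominator. Ordering by quadrant would have no finite upper limit in the non-significant case, which the text does not anticipate.

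A reader might also infer that cost saving is wrongly included whenever the effect is non-significant. That is too broad: with an uncertain cost difference, cost saving can be truly compatible with the data (step 4).

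Nor is the chance that THPP is dominated hidden. The plane shows that quadrant, and in the example the acceptability curve would level off at about 93% (100% − 6.9%), which reveals the missing upper limit. This is a fair point and lowers the stakes. It also means that a raw-ratio interval would disagree with the curve printed beside it.

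Finally, the article attaches no decision rule to the ICER interval, and the cost inputs used here are not from the article.

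**Conclusion.** The concern holds in a limited form. Applying a usual bootstrap interval to the ICER under the stated trigger would give a false finite upper limit when the effect difference is non-significant. For the PHQ-9 score that case has probability about 10% (Pakistan) and 16% (India) at the Table 4 effect, and more at smaller effects. A lower limit that misleadingly suggests cost saving additionally needs clearly higher costs, roughly 2 SE or more. With a clearly significant effect the defect is small.

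The conclusion assumes a 95% two-sided level and intervals that rank raw ratios. The illustrations also assume particular cost differences and no cost–effect correlation, and the bootstrap uses lognormal costs and individual resampling. This is a worthwhile, inexpensive improvement. It does not invalidate the economic evaluation, whose plane and acceptability curves remain sound.

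**What to change.** In the Economic analysis section, report the ICER as a point estimate. Put the 95% confidence interval on incremental net benefit, defined as willingness-to-pay × effect difference − cost difference, over the same willingness-to-pay range as the acceptability curve and from the same bootstrap replicates in all four quadrants. If limits for the ICER are wanted, take the willingness-to-pay values at which the net-benefit limits cross zero, and state that there is no upper limit where they do not cross.

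The cost is a change of wording: no new data and no further resampling. The small downside is that the interval depends on the willingness-to-pay value, which the acceptability curve already varies.

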#### Compliance analysis

A proportion of participants, in both trials, may comply poorly with the THPP intervention. A complier average causal effect analysis will be undertaken, which estimates the effect of the intervention on the participants who received it as intended by the original randomisation. This assumes that participants in the EUC arm have the same probability of non-compliance as do participants in the THPP arm. We will also adjust the analysis for contamination between arms (i.e. if participants in the EUC arm were exposed to the intervention through contact with intervention arm participants).

#### Moderator analysis

Moderator analyses will be used in both trials to help clarify on whom and under what circumstances (moderators) the THPP intervention works. We will assess modification of treatment effect by a priori defined modifiers (age group, socio-economic status, education, parity, chronicity of depression, baseline severity of depression and patient expectations), by fitting appropriate interaction terms and testing for heterogeneity of treatment effects in regression models. We will also carry out mediator analysis to see what key behaviours our intervention activated or affected that led to improved outcomes at 3 and 6 months. The hypothesised mediators include behavioural activation (assessed by the premium abbreviated activation scale), perceived social support (assessed by the multidimensional scale of perceived social support) and mother–child attachment (assessed by items of the maternal postnatal attachment scale).

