The South Asian Hub for Advocacy, Research and Education for mental health (SHARE) was established by a grant funded by the US National Institute of Mental Health (NIMH) to address these challenges. SHARE aims to adapt an established evidence-based intervention, the Thinking Healthy Programme (THP) originally developed and evaluated in Pakistan [22, 25]. THP has recently been adopted by the World Health Organisation (WHO) for global implementation (http://www.who.int/mental_health/maternal-child/thinking_healthy/en/) [26], and has now been adapted for delivery by peers (called the Thinking Healthy Programme Peer-Delivered or THPP) in India and Pakistan, through extensive formative research [27]. The peers who deliver the intervention are women with children living in the same community as the participants, and who work in partnership with established CHWs. In this paper, we describe the protocol for two concurrent randomised controlled trials being conducted in India and Pakistan, which aim to evaluate the effectiveness and cost-effectiveness of the THPP on maternal and child outcomes. Both trials have identical interventions and outcomes with some differences, which are highlighted by referring to them as SHARE Pakistan and SHARE India.

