### Analysis

The quantitative analysis will be done using STATA (version 13) following CONSORT guidelines for individually randomised and cluster-randomised trials respectively. Flow charts will include the number of participants seen at each stage of the trial, including the number screened, eligible, randomised and analysed for the primary outcome. Initial analyses will compare baseline characteristics of enrolled participants by arm and follow-up status. The outcome measures will be summarised at baseline and the 3- and 6-month postnatal follow-ups by intervention arm, summarised by means (standard deviation), medians (interquartile range) or numbers and proportions as appropriate (and including age, gender and baseline outcome score). For continuous outcomes, histograms within each arm will be plotted to assess how closely the scales follow a normal distribution to determine how to describe the outcomes and how to do the inferential analysis properly.

The primary analyses will be ITT at the 6-month follow-up visit adjusted for the baseline measure of the outcome. In the Pakistan trial, mixed-effects logistic regression models will be used to analyse binary outcomes, adjusting for village clusters as random-effects variables and Union Councils as fixed effects. In the Indian trial, peers will be adjusted for as a random effect in the analysis. Analyses of continuous outcomes will use mixed-effects linear regression, additionally adjusting for the baseline value of the outcome. Adjustments will also be made for variables for which randomisation did not achieve a balance between the two arms at baseline.

Effect sizes will be reported as: (1) crude and adjusted relative risks estimated using the marginal standardisation technique with 95 % confidence intervals for the ratios estimated via the delta method [46] for binary outcomes, (2) and as mean differences and standardised mean differences, with 95 % confidence intervals for continuous outcomes. Missing data for the outcomes will be estimated using multiple imputation [47]. Secondary analyses will include repeated measures analyses of data collected at the 3- and 6-month postnatal follow-ups, which is efficient use of all available data.

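### The moderator analysis groups age although years are recorded, and assesses seven modifiers within each trial with no combined estimate, so it uses less of the available information than it could

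*Protocol article*

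**What the plan says.** The Moderator analysis section gives the aim: "Moderator analyses will be used in both trials to help clarify on whom and under what circumstances (moderators) the THPP intervention works". It names seven "a priori defined modifiers (age group, socio-economic status, education, parity, chronicity of depression, baseline severity of depression and patient expectations" and says they will be assessed "by fitting appropriate interaction terms and testing for heterogeneity of treatment effects in regression models". Age is the only modifier whose form is fixed, and it is fixed as grouped. The Baseline assessments section records age in years.

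The section does not mention an estimate of modification that combines the two trials. The Background describes the trials this way: "Both trials have identical interventions and outcomes with some differences". The inclusion criteria, including the PHQ-9 threshold, are the same for both.

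Table 4 (Power calculations) gives power for three main effects in each trial, among them "Depression severity at 6 months (PHQ-9 score) – effect size 0.4" and "Remission at 6 months (PHQ-9 < 10) of 65 % in the intervention arm vs 45 % in the control arm". It gives none for interactions. No significance level is stated. The Analysis section reports results "with 95 % confidence intervals for continuous outcomes", from which I assume two-sided 5%.

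**The concern.** An interaction between equal halves has twice the standard error of a main effect with the same residual variance. Trials sized for main effects are therefore weak for modification unless it is large. Two choices in the text weaken them further without need. Grouping age discards information that has already been collected. Describing modification only within each trial leaves unused the gain from combining two trials with the same entry threshold, outcome measure, time point and list of modifiers.

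What is at stake is how far the analysis can meet its own aim of clarifying for whom the intervention works. The smaller trial, India, is the more exposed. The primary comparison is not affected.

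**Working it through.** **Inputs.** From Table 4 and the assumptions below it:
- Pakistan: 560 women, 40 clusters of 14, 20% loss, ICC 0.07 (intervention) and 0.05 (control). Analysed: 280 × 0.80 = 224 per arm, 11.2 per cluster.
- India: 280 women, 15% loss, ICC 0.05 in the intervention arm only, 30 peers. Analysed: 140 × 0.85 = 119 per arm.
- Main effect on PHQ-9 score: 0.4 SD.

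My assumptions: two-sided 5%; a two-level modifier that varies within clusters, so that the residual variance is 1 − ICC; equal halves unless stated.

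**Step 1. Reproduce Table 4 (effect size 0.4).**
- Pakistan: design effects 1 + 10.2 × 0.07 = 1.714 and 1 + 10.2 × 0.05 = 1.510. With a noncentral t on 38 df, power is 90.1% (stated 90%).
- India: design effect 1 + (119/30 − 1) × 0.05 = 1.148 in the intervention arm. SE = √(1.148/119 + 1/119) = 0.134, and Φ(0.4/0.134 − 1.96) = 84.5% (stated 84%).
- The remission rows give 91.6% and 81.8% in Pakistan (stated 90% and 81%) and 86.4% and 74.7% in India (stated 86% and 74%).

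All six figures reproduce within 2 points, so the inputs are read correctly.

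**Step 2. Power for an interaction.** SE = √(v_I/n + v_C/n) × √(1/q + 1/(1 − q)), where v = 1 − ICC and q is the subgroup share. At q = 0.5 the second factor is 2.
- Pakistan: 2 × √((0.93 + 0.95)/224) = 0.183
- India: 2 × √((0.95 + 1)/119) = 0.256
- Combined by inverse variance: 1/√(1/0.183² + 1/0.256²) = 0.149

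Power = Φ(d/SE − 1.96):

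| Interaction d, split | Pakistan | India | Combined |
|---|---|---|---|
| 0.2 SD, 50/50 | 19% | 12% | 27% |
| 0.3 SD, 50/50 | 37% | 22% | 52% |
| **0.4 SD, 50/50** | **59%** | **35%** | **77%** |
| 0.4 SD, 30/70 | 52% | 30% | 69% |
| 0.4 SD, 20/80 | 42% | 24% | 57% |
| 0.6 SD, 50/50 | 91% | 65% | 98% |

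An interaction of 0.4 SD means, for example, effects of 0.6 and 0.2 SD in the two halves. If the full design effect is kept instead of 1 − ICC, the 0.4 SD, 50/50 figures are 39% in Pakistan and 32% in India.

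**Step 3. Cost of grouping age.** For a normal modifier and a linear interaction, the information kept is the between-group share of the variance:
- two equal groups: 2/π = 64%
- three: 79%
- four: 86%

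The loss is 36%, 21% and 14%. The protocol does not give the number of groups. In the worst case, a median split, the power that reads 59% and 35% would be Φ(0.4/(0.183 × √(2/π)) − 1.96) = 78% in Pakistan and, likewise, 50% in India with age continuous.

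**Step 4. False modifiers.** If all seven null hypotheses hold and each test is read at 5%, independent tests give 1 − 0.95⁷ = 30.2% per outcome per trial. With a common correlation between tests of 0.2, 0.3 and 0.5, simulation gives 28.7%, 27.1% and 22.9%.

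**The case against.** The modifiers are named in advance, interaction tests are the right tool, and the analysis is explanatory. A multiplicity rule, the coding of the other modifiers and the outcome to be tested are commonly left to an analysis plan, and their absence from an article is not an error. All of that stands. The text also does not say that modifiers are tested one at a time or that 5% applies, so the 23–30% is conditional on that reading.

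The trials also differ. Pakistan randomises village clusters and India individual women. Recruitment sources differ, and Pakistan adds group sessions where India has individual sessions only. Assessing modification within each trial is therefore legitimate. This argues against making a pooled model the main test, but not against showing a pooled estimate beside the others. Grouping can also reveal a non-linear pattern, and a grouped display kept as a check meets that point.

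Some stronger readings are tempting but not supported:
- *A modifier found in one trial is more likely than not to be chance.* If one of seven is real at 0.4 SD, expected false positives are 6 × 0.05 = 0.30 and expected true ones 0.59 or 0.35. The chance share is 0.30/0.89 = 34% in Pakistan and 0.30/0.65 = 46% in India. It passes half only under weaker effects, such as 0.2 SD (61% and 72%).
- *A real modifier will usually be missed.* At 0.4 SD this is not so in Pakistan (59%), and at 0.6 SD in neither trial.
- *The false-modifier risk is 76% over both trials and two outcomes.* 1 − 0.95²⁸ treats PHQ-9 remission and PHQ-9 score as independent, although both come from one questionnaire.
- *Patient expectations in Pakistan are contaminated by allocation.* Villages are allocated before recruitment, but the recruiting teams are blind to arm and nothing says that women know it at baseline.

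**Conclusion.** The point holds as a matter of precision. The text commits to grouped age where years are available, and it describes modification only within trials that were sized for main effects. At 0.4 SD, power is about 59% in Pakistan and 35% in India, against about 77% combined. This rests on equal halves, a modifier that varies within clusters, two-sided 5% and, for the combined figure, similar modification in both countries. Uneven splits, smaller interactions or a full design effect lower the figures, and larger interactions raise them. The 14–36% loss from grouping rests on normal age, a linear interaction and two to four equal groups. The false-modifier chance of about 23–30% rests on seven unadjusted 5% tests with no true modifier.

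A reader might go on to infer that a formal correction such as Holm's method is required. The documents attach no confirmatory claim to this analysis, so labelling it exploratory is enough.

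**What to change.** In the Moderator analysis section:
1. Replace grouped age with age in years as a continuous modifier, and use a non-linear term or a grouped display as a check of its shape.
2. Add a pooled individual-participant interaction estimate, with trial as a fixed factor and each trial's own strata and random effects, beside the two trial-specific estimates.
3. State that all moderator results are exploratory, and report them with confidence intervals.

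The cost is wording and a common coding of modifiers such as education and socio-economic status. No further data on age, participants or visits are needed. The downside is that a continuous term assumes a functional form and a pooled estimate assumes similar modification in both countries. The displays beside them let readers check both.
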